## Abstract

**Background:**

Most patients with type 2 diabetes have suboptimal control of their glucose, blood pressure (BP), and lipids – three risk factors for diabetes complications. Although the chronic care model (CCM) provides a roadmap for improving these outcomes, developing theoretically sound implementation strategies that will work across diverse primary care settings has been challenging. One explanation for this difficulty may be that most strategies do not account for the complex adaptive system (CAS) characteristics of the primary care setting. A CAS is comprised of individuals who can learn, interconnect, self-organize, and interact with their environment in a way that demonstrates non-linear dynamic behavior. One implementation strategy that may be used to leverage these properties is practice facilitation (PF). PF creates time for learning and reflection by members of the team in each clinic, improves their communication, and promotes an individualized approach to implement a strategy to improve patient outcomes.

**Specific objectives:**

The specific objectives of this protocol are to: evaluate the effectiveness and sustainability of PF to improve risk factor control in patients with type 2 diabetes across a variety of primary care settings; assess the implementation of the CCM in response to the intervention; examine the relationship between communication within the practice team and the implementation of the CCM; and determine the cost of the intervention both from the perspective of the organization conducting the PF intervention and from the perspective of the primary care practice.

**Intervention:**

The study will be a group randomized trial conducted in 40 primary care clinics. Data will be collected on all clinics, with 60 patients in each clinic, using a multi-method assessment process at baseline, 12, and 24 months. The intervention, PF, will consist of a series of practice improvement team meetings led by trained facilitators over 12 months. Primary hypotheses will be tested with 12-month outcome data. Sustainability of the intervention will be tested using 24 month data. Insights gained will be included in a delayed intervention conducted in control practices and evaluated in a pre-post design.

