### CAS theory and practice facilitation

Practice Facilitation (PF) is an intervention that exploits these CAS properties and overcomes the aforementioned barriers [23,24]. PF occurs when a trained facilitator meets with staff and clinicians in each practice over several months to assist the team in addressing an issue, such as improving risk factors for diabetes complications. The facilitation is guided by insights from an in-depth multi-method assessment process in each practice prior to the facilitation intervention. Facilitation meetings create time for learning and reflection by members of the team. This in turn helps the practice team improve their communication so that they can adopt and implement a strategy to improve patient care. It has proven effective in the primary care setting for improving quality of care processes for rates of colorectal cancer screening [24], health habit counseling [25], and the quality of asthma care for children [26]. Although the effectiveness of in primary care settings has been demonstrated for process measures of quality, its effectiveness in improving clinical outcomes such as A1c, BP, or lipids for patients with type 2 diabetes has not been tested. In addition, little is known about the process through which PF might improve patient outcomes.

The purpose of the proposed group randomized controlled trial is three-fold: 1) to improve risk factors for type 2 diabetes complications across a diversity of primary care clinics through PF; 2) to examine the relationship between implementation of the CCM and communication among staff and clinicians; and 3) to advance the science of translational research in primary care settings by examining the sustainability of the intervention. The specific objectives are to:

1. Evaluate the effectiveness and sustainability of PF to improve risk factors for type 2 diabetes complications across a variety of primary care settings.

Hypothesis 1a: Patients within intervention practices will have lower A1c, blood pressure and lipid levels than those in control practices.

Hypothesis 1b: This improvement will be sustained over the 12-month period after withdrawal of the PF intervention.

2. Assess the implementation of the CCM in response to the intervention.

Hypothesis 2a: Compared to control practices, practices in the intervention group will improve their delivery of CCM elements.

Hypothesis 2b: This change will be sustained 12 months after the intervention is withdrawn.

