### Data collection

To obtain the dependent and independent variable necessary to accomplish specific aims one through three, clinician and staff surveys will be administered and medical record abstracted in each clinic. Site visits will be conducted in all 40 clinics and will be conducted three times: at baseline after enrollment but prior to randomization, and 12 and 24 months after starting the initial facilitation intervention in each clinic. During each site visit, clinicians and staff will complete surveys to measure the presence of the elements of the CCM as well as communication among clinicians and staff (see description of outcomes below).

The second method of data collection is a blinded medical record abstraction for the primary outcomes: A1c, BP, and lipid levels. This will be accomplished by a trained chart auditor who is blinded to assignment of clinics to intervention or control groups. The abstraction will take place at baseline, after the conclusion of the delayed intervention in the control clinics and 12 months after the end of the intervention in the initial intervention clinics.

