### The delayed intervention

Insights gained during the initial 12-month intervention will be used to design **a **refined and enhanced delayed facilitation intervention in the practices initially randomized to the control group. This design allows initial learning about intervention techniques to be rapidly tested in the delayed intervention practices after they have served as controls. Importantly, the design also provides an incentive for the control practices to participate, because instead of just providing control data, they later receive a refined intervention. It is also important to note that institutional review boards are increasingly questioning the ethics of not offering control subjects and settings some benefit from participation in an RCT. This delayed intervention will help address those concerns. The delayed intervention will be similar process to the PF described above. However, the knowledge and skills acquired in the first 20 practices will be used to refine and enhance both the evidence-based strategies in the facilitator toolbox. This delayed intervention will be evaluated in a pre-post design.

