### Sample size and analysis

To test hypotheses for specific aim one, the unit of randomization will be the clinic and the unit of analysis will be the repeated measure of each risk factor for each patient, nested within the clinic. The outcome will be the level of control of each risk factor. We will examine A1c as our primary outcome, with BP and LDL-cholesterol as secondary outcomes. To study change in risk factor level, a hierarchical or random effect model will be used to account for the nesting of repeated measurement of risk factor within patients and patients within clinics [46,47].

The power calculation is derived for the planned cluster randomized design with 20 clinic in each treatment arm and 40 patients each clinic under the hierarchical linear analysis plan (random effects models), and the significance level set at 0.05. For the first specific aim, our primary outcome is A1c and the power estimates are calculated based on the interclass correlation coefficient (ICC) for A1c obtained from a preliminary study of 20 practices [48]. That value is 0.113. For the first specific aim, if the mean decrease in A1c due to intervention is 0.7 or greater, then the power for detecting the intervention effect on A1c is 0.80.

For specific aims two and three, the ACIC score (for specific aim two) and the communication score (for specific aim three) measured repeatedly at the staff and clinician level will be the outcome of primary interest, as it will reflect the presence of elements of the CCM. Due to a similar distributional nature of the ACIC or communication score and risk factors (ACIC and communication scores are measured repeatedly at three time points at the staff level nested within each clinic and are continuous), the three-level random effects model as proposed for specific aim one is appropriate. Sample size and power calculations for these aims are similar to those for the first aim. For the second aim, the ICC of the ACIC score is 0.12 with a standard error of 2.15, resulting in a power of 0.94 to detect a change in ACIC score of at least 1.5 in response to the intervention. For the third specific aim, the ICC for communication scores is 0.33 and the associated standard error is 9.46, thus the power for detecting the intervention effect on communication score is no less than 0.81 if the mean communication score in the intervention group is seven points or greater compared to that for the control group.

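### Sustainability is to be tested at 24 months, when no randomised untreated comparator remains because the control clinics are due to receive an enhanced version of the same intervention

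*Protocol article*

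**What the plan says.** **Time points.** The Abstract (Intervention) sets two: "Primary hypotheses will be tested with 12-month outcome data", and "Sustainability of the intervention will be tested using 24 month data".

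**Hypotheses.** In the section CAS theory and practice facilitation, Hypotheses 1a, 2a and 3a define improvement relative to control practices. Hypothesis 1b then reads: "This improvement will be sustained over the 12-month period after withdrawal of the PF intervention". Hypotheses 2b and 3b say the same for Chronic Care Model delivery and for communication.

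**Control arm after month 12.** The section The delayed intervention describes a "refined and enhanced delayed facilitation intervention in the practices initially randomized to the control group". It follows a process similar to the first and is given once those clinics have served as controls. Its own evaluation is stated: "This delayed intervention will be evaluated in a pre-post design".

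**Final measurement.** Under Data collection, the final chart abstraction comes "after the conclusion of the delayed intervention in the control clinics" and 12 months after PF ends in the initial clinics. Outcomes gives a total of 36 months of dated values, of which 12 precede baseline. Surveys are taken at baseline, 12 and 24 months.

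**Analysis.** Sample size and analysis gives a hierarchical model for aim 1. For aims 2 and 3 it applies the same kind of model to scores "measured repeatedly at three time points at the staff level nested within each clinic". No separate contrast is named for month 24.

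**The concern.** The improvement that Hypotheses 1b, 2b and 3b expect to persist is defined against control practices. By the time persistence is measured, those practices have had, or are having, a version of the same intervention that is intended to be better. A between-arm difference at month 24 would then measure initial PF a year after withdrawal against delayed PF at about its end, which is not the question asked.

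At stake is the sustainability half of the first specific objective, with its counterparts in aims 2 and 3. A lasting benefit could be reported as lost, or as inferior to control. Conversely, a non-significant change from month 12 to month 24 within the intervention arm could be reported as proof of retention, which it is not.

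**Working it through.** **1. When are the control clinics treated?**
- Values cover 36 months in total, 12 of them before baseline, so follow-up is 36 - 12 = 24 months.
- The final abstraction follows the end of the delayed intervention and falls 12 months after the end of the 12-month initial PF: 12 + 12 = month 24.
- Controls start only after serving as controls for the initial 12 months.
- The delayed intervention therefore fits between about months 12 and 24. This is an inference, since no start month is given.

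**2. Does a later start change the conclusion?** Design has four blocks at three-month intervals, so starts at calendar months 0, 3, 6 and 9. The section The delayed intervention says that experience from the first 20 practices is used, which could mean waiting for block 4 to finish at 9 + 12 = calendar month 21. On that reading, the control clinics of blocks 1 to 4 reach their own month 24 at calendar months 24, 27, 30 and 33, after 3, 6, 9 and 12 months of delayed PF. None is untreated at month 24 on this reading either.

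**3. What would a between-arm contrast at month 24 show?** Take the protocol's A1c effect of 0.7. Let s be the share retained in the initial arm and c the delayed effect as a share of 0.7. Both are assumptions. Expected benefit of the initial arm over control: D = 0.7 × (s - c).

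| s | c | D |
|---|---|---|
| 1 | 0 (untreated control) | 0.70 |
| 1 | 0.5 | 0.35 |
| 1 | 0.75 | 0.175 |
| 1 | 1 | 0 |
| 1 | 1.25 | -0.175 |
| 0.5 | 0.5 | 0 |
| 0.5 | 1 | -0.35 |

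D is zero whenever s = c, so a null result cannot separate full retention with an equally good delayed version from half retention with a half-effective one. At D = 0 a two-sided 5% test rejects 5% of the time, 2.5% in favour of the initial arm, whatever the SD or ICC.

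The protocol's stated power of 0.80 for a 0.7 effect cannot be reproduced from its inputs, because no A1c SD is given. Nothing here depends on it.

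**4. What would a within-arm contrast show?** Let T be the secular change in A1c from month 12 to month 24. The expected change is W = 0.7 × (1 - s) + T. With s = 1 and T = 0, W = 0, as it should be. With s = 0.5, W = 0.35 + T, so a background fall of 0.35 would hide the loss of half the effect. The contrast avoids the false null in step 3 but cannot separate retention from trend.

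**5. Can the staggered starts help?** Assume delayed starts 12 months after each block's start: calendar months 12, 15, 18 and 21. Block 1 intervention clinics finish PF at month 12 and block 4 controls stay untreated until month 21, which gives 21 - 12 = 9 months of concurrent untreated data after withdrawal. Block 2 has at most 21 - 15 = 6 months, block 3 has 21 - 18 = 3, and block 4 has none. The longest comparison is five clinics against five from another randomisation block, and it stops 3 months short of the 12-month horizon.

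**The case against.** The strongest reply is that the protocol never says the arms will be compared at month 24. Withdrawal of PF applies only to the initial intervention clinics, so Hypothesis 1b can be read as a within-arm question. Saying that control clinics receive PF after serving as controls suggests that the authors no longer regard them as controls. A condensed article may leave the exact contrast and margin to a fuller document.

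Much of this stands. The false null in step 3 is conditional on a contrast the protocol does not state, and an unspecified margin alone would not be a finding. What remains is fixed by the design: no later analysis document can restore a randomised untreated arm at month 24, while the hypotheses carry forward an improvement defined against one.

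Three stronger readings are tempting, and the document does not support them.
- **That the primary effect is diluted by treated controls.** The Abstract ties the primary hypotheses to 12-month data.
- **That the model for aims 2 and 3 pools the 24-month control scores into one arm effect.** The text says only that scores are measured at three time points; an arm-by-time model would use all three without pooling.
- **That the uncontrolled pre-post design is the planned test of sustainability.** The Abstract ("Insights gained will be included in a delayed intervention conducted in control practices and evaluated in a pre-post design") and the section on the delayed intervention assign it to evaluating the delayed intervention only.

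**Conclusion.** The point holds in limited form. On the protocol's own timing, no randomised untreated comparator exists at month 24, so Hypotheses 1b, 2b and 3b cannot receive the randomised test that their wording suggests. If arms were compared then, a fully sustained 0.7 effect would have an expected difference of 0 with an equally effective delayed version, a diluted one with a weaker version, and a reversed sign with a stronger one. A within-arm comparison is workable but uncontrolled, and a non-significant change would not show retention.

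This rests on the inferred window of about months 12 to 24 (the conclusion survives the later start in step 2) and on illustrative values of s and c. A reader should not infer that sustainability cannot be studied at all, or that the 12-month result is compromised. The randomised 12-month primary test is intact.

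**What to change.** In the Abstract (Intervention) and in Sample size and analysis:

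1. State that month-24 data from control clinics are not used as an untreated comparator. Extend the 12-month limit explicitly to the between-arm tests of Hypotheses 2a and 3a, so that the reference to three time points cannot be read otherwise.
2. Test Hypotheses 1b, 2b and 3b as the month 24 minus month 12 change within the 20 initial intervention clinics, with a 95% confidence interval from the clustered model. Conclude retention only if the interval excludes a loss larger than a margin set for each outcome before the 24-month data are seen. Label the result non-randomised and open to secular trend.
3. As a supportive analysis for A1c, BP and LDL only, fit one model to the dated values from all 40 clinics, with calendar time and exposure state (untreated, on PF, after PF, on or after delayed PF), using the staggered block starts. Report that the cross-block comparison is small, reaches at most 9 months after withdrawal, and depends on an assumed delayed-start calendar. State the actual start dates. The survey scores, taken at only three visits, do not lend themselves to this.

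The cost is wording, a margin for each outcome and one extra model, with no new data. The downside is a weaker sustainability claim, stated as such.

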**Primary and secondary outcomes:**

To test hypotheses, the unit of randomization will be the clinic. The unit of analysis will be the repeated measure of each risk factor for each patient, nested within the clinic. The repeated measure of glycosylated hemoglobin A1c will be the primary outcome, with BP and Low Density Lipoprotein (LDL) cholesterol as secondary outcomes. To study change in risk factor level, a hierarchical or random effect model will be used to account for the nesting of repeated measurement of risk factor within patients and patients within clinics.

This protocol follows the CONSORT guidelines and is registered per ICMJE guidelines:

**Clinical Trial Registration Number:**

NCT00482768

## Background

Although tight control of glucose (A1c), blood pressure (BP), and lipids can prevent complications from type 2 diabetes [1-4], a substantial proportion of patients with type 2 diabetes seen in primary care settings have poor control of one or more of these risk factors [5-7]. According to the Chronic Care model (CCM), patient outcomes such as good control of these risk factors should be associated with the presence of one or more of the following elements within the health care organization: organizational leadership, self-management support, delivery system design, decision support, clinical information systems, and community linkages [8,9]. Barriers to implementing the CCM elements in primary care include a lack of motivation of key stakeholders, no external motivators for change, a paucity of resources, and no perceived opportunities to implement change [10,11].

### Assumptions behind organizational interventions

When we design or use organizational interventions to improve patient outcomes, we make assumptions about the nature of the system we are targeting. Many prior attempts to design interventions for primary care settings were based on a mechanistic approach: each practice or clinic has a broken or sub-standard 'part' that needs to be isolated and 'fixed.' These approaches have consistently provided disappointing results [12]. A recent review of such efforts revealed only a 9% improvement across all clinical practice guideline implementation studies [13]. In a review of strategies to improve glycemic control, the Agency for Healthcare Research and Quality's funded Evidence Based Practice Center identified 27 studies that employed organizational interventions [14]. They concluded: '...organizational change as a broad category had little impact on glycemic control....' What do we know about primary care teams that would inform the development of a more effective intervention to overcome these barriers in primary care settings?

### Primary care clinics are complex adaptive systems

Recent conceptualizations of the health care system of the 21st century call for recognition of the complex, adaptive nature of primary care settings [15]. Conceptualizing primary care practices as complex adaptive systems (CAS) facilitates understanding their current state, health systems context, and potential for change in response to interventions [10,16]. A CAS is a collection of individuals (*e.g.*, clinicians, staff, administrators, and patients) whose actions are interconnected such that one person's action changes the context for other individuals in the system [17]. Although these individuals can behave in unpredictable ways, they usually act according to a set of stated and unstated simple rules [18,19]. Agents in a CAS tend to repeat patterns of activities that serve their particular values and motivations, making transformation difficult because changes are met by pressures to maintain the status quo [20]. CASs have multiple feedback loops by which agents organize and reorganize based upon nonlinear interactions [21].

The ability of a CAS to adapt in a manner that allows for change or improvement can be enhanced by improving the quality and quantity (bandwidth) of communication among agents [17-19]. In a study of organizational features that support innovation in primary care practices, a key feature was an increase or improvement in communication and participation among people at all levels of the practice [11]. Another example of the importance of communication can be found in studies regarding implementation of Electronic Medical Records. (EMRs) Although EMRs are seen as potentially effective strategies to improve quality and outcome of care, a failure to resolve communication problems between agents in the system, rather than a failure to resolve information technology problems, is a major cause of failed implementation [22]. The central question for any translational research effort in primary care settings is: how can we leverage the properties of a primary care CAS to develop sustainable interventions that will improve patient outcomes across a wide diversity of primary care settings? One such approach is practice facilitation.

### CAS theory and practice facilitation

Practice Facilitation (PF) is an intervention that exploits these CAS properties and overcomes the aforementioned barriers [23,24]. PF occurs when a trained facilitator meets with staff and clinicians in each practice over several months to assist the team in addressing an issue, such as improving risk factors for diabetes complications. The facilitation is guided by insights from an in-depth multi-method assessment process in each practice prior to the facilitation intervention. Facilitation meetings create time for learning and reflection by members of the team. This in turn helps the practice team improve their communication so that they can adopt and implement a strategy to improve patient care. It has proven effective in the primary care setting for improving quality of care processes for rates of colorectal cancer screening [24], health habit counseling [25], and the quality of asthma care for children [26]. Although the effectiveness of in primary care settings has been demonstrated for process measures of quality, its effectiveness in improving clinical outcomes such as A1c, BP, or lipids for patients with type 2 diabetes has not been tested. In addition, little is known about the process through which PF might improve patient outcomes.

The purpose of the proposed group randomized controlled trial is three-fold: 1) to improve risk factors for type 2 diabetes complications across a diversity of primary care clinics through PF; 2) to examine the relationship between implementation of the CCM and communication among staff and clinicians; and 3) to advance the science of translational research in primary care settings by examining the sustainability of the intervention. The specific objectives are to:

1. Evaluate the effectiveness and sustainability of PF to improve risk factors for type 2 diabetes complications across a variety of primary care settings.

Hypothesis 1a: Patients within intervention practices will have lower A1c, blood pressure and lipid levels than those in control practices.

Hypothesis 1b: This improvement will be sustained over the 12-month period after withdrawal of the PF intervention.

2. Assess the implementation of the CCM in response to the intervention.

Hypothesis 2a: Compared to control practices, practices in the intervention group will improve their delivery of CCM elements.

Hypothesis 2b: This change will be sustained 12 months after the intervention is withdrawn.

Hypothesis 2c: Implementation of the CCM elements will be associated with risk factor control, but this association will be stronger in the intervention clinics.

3. Examine the relationship between communication within the practice team and the presence of the CCM elements.

Hypothesis 3a: Communication among staff and clinicians within intervention clinics will improve compared to control clinics.

Hypothesis 3b: This improvement in communication will be sustained 12 months after the intervention is withdrawn.

Hypothesis 3c: Communication among staff and clinicians will be associated with a change in the presence of the CCM elements, but this association will be stronger in intervention clinics.

4. Determine: the cost of the intervention from the perspective of the organization providing the PF intervention activities; the net cost (revenue minus cost of services and intervention) from the perspective of a primary care practice; and the costs per change in risk factor from each perspective. (This objective is descriptive. No hypotheses are postulated.)

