For the fourth specific aim, a project accounting system will be developed to allocate all project expenses to a set of cost categories (cost pools) to assess the cost from the perspective of the organization conducting the intervention. Definitions and rules for assigning expenses into cost pools will be developed by the PI and project director in the first three months of the project. The second goal of specific aim four is to estimate the direct variable cost of conducting PF in the typical primary care facility. Net cost to the practice of implementing the intervention is: Revenues – (service cost plus cost resulting from intervention). Revenue will be tracked from billing data downloaded from each practice during each of the three site visits to track utilization and charges for all patients with type 2 diabetes in each practice for the 12 months prior to intervention, and at the end of 12 month period following the first facilitation visit. The methods used to collect cost data include meeting with the office manager at each practice during each site visit, and the collection of detailed field notes by the facilitators during direct observation in each practice. These data will be used to estimate the fixed and incremental cost of all resources used by the practice to implement the new strategy. We anticipate that these new resources will vary from practice to practice depending on the number of strategies implemented by the practice as a result of the intervention.

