For specific aim four, the difference in revenues generated by the practice for all services provided to patients with diabetes for the 12 months prior to the intervention compared to the 12 months during the facilitation intervention will be determined. Second, the cost of providing services to each patient with diabetes in each practice will be estimated using CPT codes for services delivered at that CPT codes Relative Value Units from MedPar files [49]. Finally, the incremental cost of implementing the strategy to improve risk factor control in each practice will be estimated.

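### The practice's net cost is defined as revenue minus costs, so the practice-perspective cost per change in risk factor has the wrong sign; separately, the revenue change is stated only as an uncontrolled before/during difference

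*Protocol article*

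**What the plan says.** Objective 4 (end of the section CAS theory and practice facilitation) asks for three things. The first is the cost to the organization that provides facilitation. The second is "the net cost (revenue minus cost of services and intervention) from the perspective of a primary care practice". The third is a set of ratios built on these two quantities, described as "the costs per change in risk factor from each perspective". The objective is labelled descriptive and has no hypothesis attached.

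Data collection gives the practice quantity as a formula: "Net cost to the practice of implementing the intervention is: Revenues – (service cost plus cost resulting from intervention" (the bracket closes there). For the organization, "a project accounting system will be developed to allocate all project expenses to a set of cost categories (cost pools" is the source of cost, and no revenue enters.

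On revenue, Data collection says: "Revenue will be tracked from billing data downloaded from each practice during each of the three site visits". The follow-up period for billing runs for 12 months from the first facilitation visit. The same section places three site visits in all 40 clinics.

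Sample size and analysis describes the aim 4 revenue analysis as a contrast of two years: revenue "for the 12 months prior to the intervention compared to the 12 months during the facilitation intervention will be determined". It names no control comparison. It next says that service cost per patient with diabetes and the incremental cost of the strategy will be estimated, and gives no between-period or between-arm contrast for either.

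**The concern.** There are two separate problems.

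**Sign.** A net cost should be positive when the practice ends up paying and negative when it ends up gaining. The stated formula does the reverse, in both places where it appears, so it is not a slip in one sentence. The quantity is also carried forward: it is the practice-perspective numerator of the cost per change in risk factor (A1c, BP and lipids). A table showing that ratio beside the organization's would hold two figures with the same name. A positive value would mean money spent in one and money gained in the other.

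**Contrast.** A before/during difference within facilitated practices contains everything that changed over that year: fee schedules, coding habits, payer and case mix, price inflation. Without a concurrent comparison, all of it is read as the effect of facilitation. The trial has 20 randomized control clinics, and the visit and billing arrangements suggest that their revenue could be observed over the same period.

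**Working it through.** The article states no revenue, cost or ratio figure, so there is nothing to reproduce. All money amounts below are assumed units, used only to show direction.

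**Inputs from the protocol article**
- Practice quantity: revenue R minus (service cost S plus intervention cost I) (Objective 4; Data collection).
- Organization cost: project expenses in cost pools, with no R (Data collection).
- A1c decrease of 0.7: the effect used for power (Sample size and analysis), taken here as an example denominator with improvement counted as positive.
- Revenue contrast: 12 months before against 12 months during facilitation (Sample size and analysis).
- Site visits in all 40 clinics, and billing downloads from each practice at each visit (Data collection).
- Four blocks of ten clinics, with facilitation starting in groups of five at three-month intervals (Design).

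**Step 1: sign of the practice quantity.**
Plan: N = R - (S + I). Usual net cost: C = (S + I) - R. Hence C = -N, whether the terms are annual levels or changes between years.

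| R | S | I | Plan's net cost N | Usual net cost C | N / 0.7 | C / 0.7 |
|---|---|---|---|---|---|---|
| 100 | 90 | 5 | 100 - 95 = +5 | -5 (a gain) | +7.14 | -7.14 |
| 100 | 98 | 5 | 100 - 103 = -3 | +3 (a loss) | -4.29 | +4.29 |
| 100 | 95 | 5 | 100 - 100 = 0 | 0 | 0 | 0 |

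Except at break-even, the sign flips and the size does not change.

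**Step 2: the organization-perspective ratio.**
With an assumed organization cost of 20, the ratio is 20 / 0.7 = 28.6. R does not appear, so the definition of net cost cannot affect it. If the A1c change were entered as -0.7, both perspectives would change sign together and would still disagree in convention.

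**Step 3: before/during against controlled difference.**
Before/during: (during - before) in intervention clinics. Controlled: (during - before) in intervention clinics minus (during - before) in control clinics. Assume intervention-clinic revenue goes from 100 to 110.

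| Change in control clinics | Before/during | Controlled |
|---|---|---|
| 0 | +10 | 10 - 0 = +10 |
| 5 | +10 | 10 - 5 = +5 |
| 10 | +10 | 10 - 10 = 0 |
| 15 | +10 | 10 - 15 = -5 |

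The before/during figure is the same in all four rows, so it cannot tell them apart. Background growth in service cost would offset part of background growth in revenue within the net figure. The correction therefore has to cover both terms.

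**Step 4: are control data available?**
Visits in all 40 clinics, together with billing downloads from each practice at each visit, imply that control-clinic revenue will be collected. The follow-up window, however, is dated from the first facilitation visit, and control clinics have none in the first year. The block structure supplies a substitute date: the start of facilitation in the same block.

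**The case against.** The strongest reply is that the sign is a matter of labelling. The formula is written out twice and consistently, so anyone computing it knows what is subtracted from what. The result is exactly -1 times the usual quantity, no information is lost and no estimate is biased. That is correct, and it is why a change of wording is enough. It does not remove the problem, because the article calls the quantity a cost and places it beside a true cost in a pair of ratios.

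On the contrast, the reply is that three sentences in a condensed article do not exclude a control comparison, and that the full protocol may contain one. This stands in part: the article does not say that control clinics are left out. But it does name a contrast, and the one it names is within-practice. Followed as written, it leaves background change in the result.

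Four stronger readings are tempting, and the document does not support them:
- **That every cost-per-risk-factor ratio is reversed.** Only the practice-perspective ratios use net cost.
- **That the plan would rank the costliest practices as the cheapest.** No ranking of practices is planned.
- **That the ratio divides an uncontrolled cost by a controlled A1c effect.** The article does not define the change in the denominator. It may be a between-arm or a within-practice change.
- **That control clinics are stated to supply matching billing data.** This is an inference from two statements, and the follow-up window for controls still needs a start date.

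**Conclusion.** Both parts hold within these limits. The practice's net cost is defined with its sign reversed, and the practice-perspective cost per change in risk factor carries that reversal. The error is complete in sign and nil in magnitude.

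The stated revenue contrast does not separate facilitation from background change. The size of that error cannot be given from the document. It equals the background change in the facilitated clinics, which the control-clinic change estimates. In the assumed range above, that is enough to leave the effect intact, halve it, remove it or reverse it.

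The second part rests on two assumptions: that each practice in the billing sentence includes the control clinics, and that no control comparison is specified elsewhere. The consequences are limited to objective 4, which is descriptive. The primary outcome, the hypothesis tests and the sample size are untouched. It should be corrected because descriptive cost figures are read at face value.

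**What to change.** 1. In Objective 4 and in Data collection, define net cost as (service cost + intervention cost) - revenue. Alternatively, keep the formula and call it net revenue. In either case, state the sign of the practice-perspective ratio, including whether a fall in the risk factor counts as positive.
2. In Sample size and analysis, estimate the change in revenue, and likewise in service cost, as the difference between the intervention year and the prior year in intervention clinics, minus the same difference in control clinics before their delayed intervention.
3. Date the control window from the start of facilitation in the clinic's randomization block, and state that the billing downloads cover control clinics for both 12-month periods.

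The first change is wording only. The second and third need a small extra analysis of data whose collection the article implies, plus a rule for the control dates. The controlled difference will be noisier than a before/during difference, which is the price of removing background change.
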